### Conceptional Framework

The novelty of this study and the planned DA is that it targets patients with different types of advanced cancer in order to provide them with information and help them decide about the continuation or forgoing of tumor-specific therapy in clinical situations, in which there is no further standard tumor-specific therapy available but treatment is available as off-label treatment or part of a trial. Hence, the DA aims to facilitate SDM, which is essentially the communication of the best-available research evidence on benefits and harms of options and the clarification of patients’ treatment preferences in relation to this information [41]. Based on a consensus of experts in the field [41], SDM has been defined in terms of 3 broad phases: (1) team talk: work together, describe choices, offer support, and ask about patients’ goals; (2) option talk: discuss alternatives using risk communication principles; and (3) decision talk: get to informed preferences, make preference-based decisions.

The DA in our project is used to influence phase 1 of the SDM, which will probably affect the health care provider-patient communication in phases 2 and 3 as well. Based on the available body of randomized trials on clinical DAs [20], we primarily expect decreased patient decisional conflict and an increased feeling of being informed. Although the impact of DAs on professional performance seems limited overall, the use of the DA with patients with advanced cancer may also reduce intensive treatment. While we will measure quality of life in our study, we do not expect changes as a result of the use of the DA based on the available research evidence [20]. Given the practice-based character of the study, we did not specify and measure psychological factors and processes that may be affected by the DA, such as coping mechanisms.

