### Design and Settings

First, patients will be recruited in a baseline phase lasting 4 months to observe usual care without using the DA. It means that oncologists will inform patients about further treatment options for cancer-specific therapy, side effects, and potential benefit, but they will not explicitly address that best supportive care would also be an option and will not use a decision support tool for eliciting patient preferences and assisting in decision making. The baseline phase will be followed by an intervention phase lasting 6 months. Oncologists and patients will use the DA in the same situation (change of treatment needs to be discussed with the patient because of disease progression, treatment toxicity, or other reasons). A minimum of 40 doctor-patient encounters will be included in the 4-month baseline, and 40 doctor-patient encounters will also be included in the 6-month DA intervention phase. The whole sample will encompass 80 doctor-patient encounters. The planned sample size is largely determined by the feasibility of recruiting patients within the available project duration.

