### Measurements

The potential effect of the DA will be evaluated by testing the improvements on the primary outcome for our study level of decisional conflict. Level of decisional conflict will be measured with the Decision Conflict Scale [55] that assesses patients’ perceptions of uncertainty, modifiable factors contributing to uncertainty, and ultimate satisfaction with the choice. It is one of the most robust and validated instruments to test the impact of DAs in end-of-life decision making [56]; We assume that the Decisional Conflict Scale score will decrease for the patients who use the DA.

Furthermore, we aim to assess the patients’ involvement in decision making, certainty about choice, and satisfaction with the oncologist-patient interaction as exploratory endpoints. Patients’ involvement in decision making will be assessed with the German questionnaire on shared decision making (PEF-FB-9) [57]. The trade-off between patients’ preferences for quality and length of life will be assessed with the validated German version of the Quality-Quantity Questionnaire [1]. The preferred role of the patient in decision making will be assessed with the German version of the Control Preference Scale [58]. Satisfaction with the oncologist-patient interaction will be assessed using the validated Questionnaire on the Quality of Physician-Patient Interaction (QQPPI) [59]. Effect on hope (German version of the Herth Hope Index [60]), anxiety (EQ-5D-5L [61]), quality of life (EORTC QLQ-C30 [62]), and documentation of patient preferences will be measured.

Description of the measures and their psychometric properties, scoring, and interpretation are provided in Table 1.

Such determinants of quality of palliative care as time of integration of specialized palliative services into care, aggressiveness of therapy (anticancer treatment <14 days before death), and place of death will be recorded.

During data collection, patients might have changes in mental status (ie, develop depression or cognitive problems) as well as experience changes in decision making. The study physician involved with data collection will document all possibly relevant factors.

The questionnaires will be completed by patients and oncologists before and after the intervention and will take approximately 15-20 minutes to complete. All assessments will be conducted in German.

**Table 1 table1:** Description of the measures and their psychometric properties, scoring, and interpretation.

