### Data Analysis

Analyses will be performed using SPSS v.20.0. A descriptive analysis of the sample will be performed. According to the level of variables, means, SDs, medians, minimum and maximum, and absolute or relative frequencies will be reported.

Clinically significant decisional conflict will be calculated and defined by a score of ≥25/100 on the Decision Conflict Scale, which is the most commonly used threshold to distinguish a harmful level of decisional conflict [62-64].

We will compare primary and exploratory outcome measures between the 2 patient groups (baseline and intervention) using Student *t* tests or analysis of variance. Parametric or nonparametric statistics (depending on the distribution of the data) will be used for the analysis of the patient groups from the baseline and intervention phases.

We will compare clinical confounders (time of integration of specialized palliative services into care; aggressiveness of therapy [anticancer treatment <14 days before death and place of death]) between the 2 patient groups (baseline and intervention) by comparing mean values. Measures of variability (SD) will be calculated.

Given the practice-based character and the small sample size of the study, we refrain from extensive measurement and multivariate analysis of mediators and moderators of the intervention effects. For the latter reason, we do not plan to use multiple imputation of missing values. Missing values will be handled by allowing a maximum of 35% missing in the calculation of scale scores.

*P* values of the corresponding statistical tests comparing treatment groups (ie, 2-sample *t* tests for continuous variables and chi-square tests for categorical data) will be given. Statistical significance will be assessed at the level of α=.05 (two-sided).

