### Timeline of the Study

The study will be conducted over a period of 3 years, with 12 months for conducting focus groups, interviews, and developing the first version of the DA. In a further 12 months, DA testing will follow as well as the completion of the DA. In the last 12 months of the study, a pre-post study and acceptance analysis will be conducted.

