## Results

We anticipate that this study will provide evidence about the developmental process, acceptance, and potential effects of a DA to support advanced cancer patients’ decision making in relation to the limitation of cancer-specific treatment near the end of life. The results will be disseminated through publications in peer-reviewed scientific journals and via presentations at academic conferences. The scoping literature review will provide information on the possible content, features, structure of DAs, and information on fostering and hindering factors in design and implementation strategies. The focus groups will identify factors influencing the decision-making process in advanced cancer, timing, and possible ways of delivery of the DA. Interviews with patients will provide information about patients’ decisional and informational needs, important factors for the decision-making process, and patient preferences and wishes regarding a DA.

Design and field testing will produce an optimized prototype of the DA for further testing. The pre-post study will test the potential effects of the DA on patients’ knowledge, behavioral changes, and clinical outcomes as well as its acceptance.

The field testing is scheduled for April 2021 to August 2021, with the final revision scheduled for September 2021. The pre-post study of the DA and acceptance testing is scheduled to start in October 2021 and shall be finished in September 2022.

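### Three end-of-life care measures that arise after the decision aid are labelled confounders and compared by means, which suits neither place of death nor a time cut off by death or end of observation

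*Protocol article*

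**What the plan says.** The Measurements section for the pre-post study introduces the items as measures of care quality that will be recorded: "Such determinants of quality of palliative care as time of integration of specialized palliative services into care", together with anticancer treatment within 14 days of death and place of death. The Data Analysis section gives the same items another role: "We will compare clinical confounders (time of integration of specialized palliative services into care; aggressiveness of therapy". It compares them between the baseline and intervention groups by mean values, with SDs. The same section also names frequencies among its descriptive statistics and chi-square tests for categorical data.

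The Conceptional Framework section expects that "the use of the DA with patients with advanced cancer may also reduce intensive treatment". The Results section lists clinical outcomes among the things on which the pre-post study will test potential effects.

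On timing, Design and Settings says "First, patients will be recruited in a baseline phase lasting 4 months to observe usual care without using the DA", then "The baseline phase will be followed by an intervention phase lasting 6 months". The Results section says the pre-post study "is scheduled to start in October 2021 and shall be finished in September 2022", and the Timeline says "In the last 12 months of the study, a pre-post study and acceptance analysis will be conducted". The article states no data cut for deaths or referrals, no observation window per patient, no time origin and no denominator for these items.

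**The concern.** There are three linked problems in what the Data Analysis section fixes.

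- **Label.** A confounder precedes or stands apart from the intervention. These items follow it, and the article itself expects the DA may reduce intensive treatment. Under the confounder label, a difference between phases would be read as imbalance between the groups and not as a possible effect.
- **Statistic.** Place of death is categorical. Time to integration is observed only in patients who are referred before they die and before observation ends, so a plain mean describes a selected subset.
- **Comparison.** Patients in the later phase enter later. If observation stops on one date for everyone, only their early referrals are seen and their mean time is pulled down whether or not the DA does anything.

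The article attaches p values at two-sided 0.05 to its group comparisons, so an artefact of this kind could be reported as a finding on end-of-life care.

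**Working it through.** **Inputs from the article.** Baseline phase 4 months, then intervention phase 6 months; 40 encounters per phase; start October 2021, end September 2022 (12 months); two-sided 0.05.

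**Assumptions not in the article.** Uniform entry within each phase; one data cut for both phases; exponential survival with median 4, 6 or 9 months; exponential time to palliative integration with median 4 months; 30% of decedents treated within 14 days of death; no DA effect at all.

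**Step 1, follow-up.** Count months from October 2021 and cut at month 12.
- Baseline entry at months 0-4: follow-up from 12 - 4 = 8 to 12 - 0 = 12 months, mean 10.
- Intervention entry at months 4-10: follow-up from 12 - 10 = 2 to 12 - 4 = 8 months, mean 5.

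**Step 2, mean time to integration among those integrated (median survival 6).** Let r = ln2/4 = 0.1733 (integration), l = ln2/6 = 0.1155 (death) and s = r + l = 0.2888. Follow-up f is uniform on (a, b). Put

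A = average of exp(-sf) = [exp(-sa) - exp(-sb)] / [s(b - a)]

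B = average of sf·exp(-sf) = [(1 + sa)exp(-sa) - (1 + sb)exp(-sb)] / [s(b - a)]

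Share integrated = (r/s)(1 - A). Mean observed time = (1 - A - B) / [s(1 - A)].

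- Baseline, (8, 12): A = 0.0588, B = 0.1635. Share = 0.6 × 0.9412 = 0.56. Mean = 0.7777 / (0.2888 × 0.9412) = 2.86 months.
- Intervention, (2, 8): A = 0.2666, B = 0.3214. Share = 0.6 × 0.7334 = 0.44. Mean = 0.4120 / (0.2888 × 0.7334) = 1.95 months.

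This agrees with simulation (2.86 versus 1.94). The gap of about 0.9 month arises with no effect present.

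**Step 3, across survival medians, cut at month 12, no DA effect** (2,000 simulated trials of 40 per phase for each setting; t test for time to integration, baseline / intervention values).

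| Median survival | Known dead | Mean time to integration, months | False-positive rate |
|---|---|---|---|
| 4 months | 82% / 56% | 2.6 / 1.8 | 0.16 |
| 6 months | 68% / 43% | 2.9 / 1.9 | 0.24 |
| 9 months | 54% / 31% | 3.1 / 2.0 | 0.30 |

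Nearly all of these rejections point to earlier integration under the DA.

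**Step 4, how much depends on the data cut** (same test, range over the three survival medians).

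| Data cut | False-positive rate |
|---|---|
| Month 10 | 0.24-0.41 |
| Month 12 | 0.16-0.30 |
| Month 18 | 0.05-0.09 |
| Month 24 | 0.04-0.06 |
| Equal window of 2 or 6 months per patient | 0.04-0.06 |

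**Step 5, direction for the other quantities** (cut at month 12, no DA effect).
- Treatment within 14 days of death, counted over all patients: 0.30 × share known dead. At median survival 6 this is 0.30 × 0.68 = 20% versus 0.30 × 0.43 = 13%, which favours the DA. The false-positive rate is about 0.15.
- The same item among decedents: 30% versus 30% if the risk is constant. If the risk falls with time since the decision, 28% versus 34% in the example run, which goes against the DA.
- Time from integration to death: 3.3 versus 1.9 months, which looks shorter under the DA.

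**The case against.** The strongest reply is that unequal follow-up is inferred. The article gives phase lengths and project dates but no data cut, and the full protocol may set a fixed window per patient or a later ascertainment date. Step 4 shows that this matters: at month 24, or with equal windows, the artefact is gone. That stands, and the size given here is conditional on a cut near the stated end. Month 24 is, however, a year past that end.

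A reader might infer that the planned comparison will produce a false DA benefit. The documents do not support that. The result depends on the cut, the time origin and the denominator, none of which is stated, and Step 5 shows that the bias can also be absent or point to harm.

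A reader might also infer that adjusting for these items would remove part of a true effect. No adjusted model is planned; the section refrains from multivariate analysis of mediators and moderators, and the items are only compared between groups.

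Nor do the documents show that every Jena patient is already integrated at enrolment. Recruitment there is in specialized palliative care, but patients under standard palliative care only are excluded.

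The general rules on frequencies and chi-square tests soften the point for the two categorical items, and the mean of a yes/no item is a proportion. Those rules still sit beside a sentence that prescribes means for exactly these variables, and they do nothing for the time variable.

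Lastly, this is a pilot, and these items are not among its named endpoints. That bears on severity.

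**Conclusion.** The point holds in limited form. The confounder label is wrong on the article's own account of what the DA may change. Means with SDs do not suit place of death, or a time cut off by death and end of observation. These two conclusions need no assumption.

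The bias is conditional. With one data cut at about September 2022, and the assumed survival and referral times, time from enrolment to integration shows a spurious gap of about 0.7 to 1.1 months (2.6 - 1.8 = 0.8 before rounding of inputs, 2.86 - 1.95 = 0.9, 3.1 - 2.0 = 1.1) and a false-positive rate of about 0.16-0.30. A later cut or equal windows bring the rate to nominal. For treatment near death the direction is open.

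Severity is minor to moderate: decisional conflict, the primary outcome, is untouched.

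**What to change.** - Call the three items exploratory outcomes in both the Measurements and Data Analysis sections.
- For palliative integration, replace the comparison of means with cumulative incidence from enrolment, censored at data close, with death as competing event, in patients not already receiving specialized palliative care at enrolment.
- Report treatment within 14 days of death and place of death as proportions among deaths, with the number of deaths, using the same observation window per patient in both phases.
- State the time origin, the denominator and the date of data close.

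The cost is some rewording, slightly more analysis and fewer deaths counted. If data close in September 2022, the longest window that every intervention patient completes is about 2 months. Expected deaths in that window are 40 × [1 - 2^(-2/median)]: about 12, 8 and 6 per phase at median survival 4, 6 and 9 months. With so few, these proportions should be descriptive only, without tests. A later ascertainment date for deaths would lengthen the common window.

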### Timeline of the Study

The study will be conducted over a period of 3 years, with 12 months for conducting focus groups, interviews, and developing the first version of the DA. In a further 12 months, DA testing will follow as well as the completion of the DA. In the last 12 months of the study, a pre-post study and acceptance analysis will be conducted.

## Results

We anticipate that this study will provide evidence about the developmental process, acceptance, and potential effects of a DA to support advanced cancer patients’ decision making in relation to the limitation of cancer-specific treatment near the end of life. The results will be disseminated through publications in peer-reviewed scientific journals and via presentations at academic conferences. The scoping literature review will provide information on the possible content, features, structure of DAs, and information on fostering and hindering factors in design and implementation strategies. The focus groups will identify factors influencing the decision-making process in advanced cancer, timing, and possible ways of delivery of the DA. Interviews with patients will provide information about patients’ decisional and informational needs, important factors for the decision-making process, and patient preferences and wishes regarding a DA.

Design and field testing will produce an optimized prototype of the DA for further testing. The pre-post study will test the potential effects of the DA on patients’ knowledge, behavioral changes, and clinical outcomes as well as its acceptance.

The field testing is scheduled for April 2021 to August 2021, with the final revision scheduled for September 2021. The pre-post study of the DA and acceptance testing is scheduled to start in October 2021 and shall be finished in September 2022.

## Discussion

The key strength of this study is that it aims at developing a DA that can be effectively used across different types of cancer. Furthermore, a wide range of topics relevant for advanced cancer near the end of life such as forgoing cancer-specific therapy and patients’ inclusion in clinical trials will be covered. To our knowledge, it will be the first DA of its kind.

In trying to develop a DA that is suitable for patients with any cancer type, this certainly will create a number of challenges (in terms of synthesizing the evidence on advanced cancer treatment options and presenting the benefits and risks and choices available). To face this challenge, 2 extensive validation validity phases will be included (review and re-draft of prototype versions 2 and 3), during which the DA will undergo review from advanced cancer patients, oncologists, and other experts from medical ethics and social sciences.

A further strength of this study is that we do not focus solely on the development of a DA but also on testing its impact on clinical practice and on patients’ health outcomes. Additionally, we will evaluate the acceptance of the DA within the implementation study.

Furthermore, for all phases of the DA development and testing, interdisciplinary experts from psycho-oncology, sociology, oncology, palliative medicine, and medical ethics will be involved, enabling a better framework for this process.

This study has several limitations. One of the limitations is that developing and subsequent testing of the DA will take place mainly at the NCT in Heidelberg. The NCT is a national innovative tumor center, combining patient-oriented research, care, and a multidisciplinary approach. It offers a wide spectrum of consulting services for patients such as nutrition, psycho-oncology, pain therapy, pastoral care, self-help, social service, sports, and physical activity. It means that patients have additional services and a more individualized care approach in comparison to other hospitals.

Although the perspective of another hospital (palliative care unit in Jena) will be taken into consideration, it is likely that future multicentric research evaluating our DA’s impact on patients’ outcomes as well as process evaluation of the DA implementation may therefore also be needed.

Furthermore, due to recruitment difficulties, we decided not to interview patients’ family members, who usually are involved in these decisions. Missing this important perspective might have an impact on the results of our study.

In patient interviews, we used a case scenario that might increase social matching bias. Furthermore, there can be a difference between what people think they would do in a described situation and their actual behavior. Furthermore, the interview guide had to be modified and customized according to the patients’ current physical and mental status. This could lead to decreased generalizability of the results.

Our sample size in the pre-post study is relatively small due to the severe conditions of the patients who are near the end of life. This leads to difficulties in recruitment and can restrict the interpretation of the results.

Furthermore, given the relatively small sample size of the planned study, we can only explore the diversity of patients and health care professionals to a specific degree.

## Abbreviations

COREQ: consolidated criteria for reporting qualitative research
DA: decision aid
IPDAS: International Patient Decision Aid Standards
NCT: National Center of Tumor Diseases
OADRI: Ottawa Acceptability of Decision Rules Instrument
PRISMA-ScR: Preferred Reporting Items for Systematic Reviews and Meta-analysis Extension for Scoping Reviews
QQPPI: Questionnaire on the Quality of Physician-Patient Interaction
SDM: shared decision making
